#### Cardiovascular health evaluation

As successfully applied in previous studies [18, 21], healthy lifestyle will be measured by the AHA’s seven health metrics (adapted by Lloyd-Jones [11] and Daniels [28]). Every health metric except smoking is categorized into ideal, moderate and poor health as defined in Table 4. Healthy diet is defined by the AHA based on expert opinion and on the dietary approach to stop hypertension (DASH) score. One point is scored for each of the following components: consumption of at least four portions of vegetables and fruits per day, at least three portions of fiber-rich nutriments per day, of fish at least two-times a week, a salt-free or salt-poor diet (less than 1.5 g/day) and not more than 1 Liter of sugar-rich drinks per week (max. 450 kcal/week) [11].

**Table 4 Tab4:** ‘Seven AHA health metrics’

Health behavior goal:	Poor	Moderate	Ideal health
Smoking-habits	Smoked in the last 30 days	–	Never smoked, never smoked a whole cigarette
Body-Mass-Index	>95th percentile	85-95th percentile	<85th percentile
Physical activity	None	< 60 min moderate or intensive physical activity per day	≥ 60 min moderate or intensive physical activity per day
Healthy diet	0–1 components	2–3 components	4–5 components
Total-cholesterol	≥200 mg/dL	170–199 mg/dL	< 170 mg/dL
Blood pressure	>95th percentile	90-95th percentile or ≥ 120 systolic or ≥ 80 diastolic	<90th percentile
Fasting blood sugar	≥126 mg/dL	100–125 mg/dL	< 100 mg/dL

Table 4 contains the definition of poor, intermediate and ideal cardiovascular health according to the seven AHA health metrics adapted from [11] and [28]

### Intervention

Our health promotion program is based on (1) enhancing the knowledge about CVDs and related risk factors, (2) medical counseling and discussion of individual risk conditions and lifestyle, (3) providing a self-assessment tool to control and visualize chances in CVD risk conditions and (4) involvement of participants in the planning of health promotion projects.

Our health-promotion program will combine the running health-promotion programs “Gesunde Schule (healthy school)” and “Do-it-yourself!” of the Tyrolean regional medical insurance company (Tiroler Gebietskrankenkasse, TGKK) with the medical examinations of the EVA-Study and health information focusing on CVDs: Potential participants are introduced into the topic of cardiovascular health in a stepwise way. First, adolescents will receive information on the aims of the EVA-project including healthy lifestyle in their school or company (kick-off event). The concept of vascular ageing as a result of continuous accumulation of cardiovascular risks from early life on will be presented orally and by written information material (flyers). The individual visualization of the vessel wall and blood pressure measurement during medical examination will help the adolescents to link this information to their own body. In a second step, individual risk behaviors and laboratory results will be discussed with each participant. In a third step, the summary result from each school/company class will be presented and compared to other schools/companies.

We will create and provide online tools to promote health among adolescents. A website will be designed with information on healthy lifestyle and will contain an encrypted, password-protected web-app that provides the participants with individual health data. Traffic-lights will be used to represent the seven health metrics defined by the AHA [7, 32]. When adding current personal information on body weight, smoking status or physical activity the colors of the traffic lights will switch from red to green (or vice versa) in order to encourage further health-improvements. Further health games (e.g. health quiz) will be added to the website.

Participants will have the opportunity to record their own physical activity over 7 days using modern movement-trackers (Move 3, Movisense GmbH, Karlsruhe, Germany). The results of these records will be downloadable from the web-app.

Special health-promotion programs of the TGKK will include behavioral- and circumstance-oriented activities specially designed for each school/company. Representatives of each school/company are invited for an afternoon workshop aiming at health promotion by oral presentations and written information material. The scholars will undergo an interview to define their interests and expectations. The results of these workshops and the interview will pick out the most relevant topics for a tailored health promotion program for each school or company class. Local health-promotion projects will be supervised by the TGKK and presented on the EVA website as a health promotion book.

### Outcome measures and statistical analysis

The *primary outcome measure* will be the difference in the proportion of each of AHA’s seven health metrics in the ideal range between the intervention and the control group.

The *secondary outcome measure* will be the change in the proportion of AHA’s seven health metrics in the ideal range between baseline and follow-up in the intervention group.

*Further descriptive and exploratory analysis* will focus on the prevalence of unfavorable health behaviors, the prevalence of vascular risk conditions and the change of these factors over age as well as their influence on EVA measured by IMT and the PWV. In addition, the influence of premature birth and early life weight gain (taken from the mother-child-booklet) on obesity and other components of the metabolic syndrome in youth will be explored.

Differences in proportions of the individual health metrics in the ideal range between the intervention and control group (primary outcome parameter) will be analyzed by Chi-squared test. The Prevalence of the individual health metrics in the ideal range in a similar cohort [18] varied from < 5% for ideal diet, over around 50% for ideal physical activity to > 80% for ideal body-mass index. On the basis of a 3:1 intervention to control group split, power analysis indicates that 95% power can be achieved with a sample size of 2000 to detect differences in proportions between intervention and control group of 3% (at a control group proportion of 96%) to 10% (at a control group proportion of 50%) [33] .Multivariate analysis will be done by logistic regression.

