**Methods:**

The EVA-Tyrol study is a population-based non-randomized controlled trial that will prospectively enroll 2000 participants from high schools and training companies in North- and East-Tyrol (Austria) and South-Tyrol (Italy). Participants will be assigned to either an intervention (*n* = 1500) or a control (*n* = 500) group. Intervention group participants will be enrolled at the 10th school grade (mean age 15–16 years), undergo two examinations within a two-year interval, with follow-up at the 12th grade (mean ages 17–18 years). Control group participants will be enrolled at the 12th grade (mean age 17–18 years). Medical examination will include anthropometric measurements, comprehensive lifestyle and dietary questionnaires, a fasting blood sample, high-resolution ultrasound of the carotid arteries, and measurement of carotid-femoral pulse wave velocity. Active intervention will consist of (1) enhancing knowledge about CVDs, (2) individual medical counseling based on the results of the baseline examination, (3) an online health promotion tool and (4) involvement of participants in planning and implementation of health promotion projects. Effectiveness of the intervention will be assessed by comparing the proportion subjects with ideal health metrics as defined by the American Heart Association between study groups.

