## Methods and design

### Study design

The EVA-study is a non-randomized controlled trial. Two thousand participants will be recruited from high schools and training companies spread over North- and East-Tyrol (Austria) and South-Tyrol (Italy). Study participants will be assigned to i) health intervention group (*n* = 1500) or ii) control group (*n* = 500). For participants included in the intervention group two examinations will be scheduled within a two-year interval between the examinations. Participants will be in the 10th grade (mean age, 15–16 years) at the baseline and in the 12th grade (mean age, 17–18 years) at the follow-up examination. Between the examinations the health intervention program will be offered.

Five hundred participants with a mean age of 17–18 years without participation in a health promotion program will serve as a control group. The prevalence of AHA health metrics in the intervention group will be compared to the prevalence in the control group (Fig. 1).

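### Seven co-equal primary tests have no multiplicity control or success rule, and the 95% power is per metric with no allowance for a seven-fold correction

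*Protocol article*

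**What the plan says.** The section on outcome measures and statistical analysis defines the primary outcome as the difference in proportion, taken metric by metric, for the AHA's "seven health metrics in the ideal range between the intervention and the control group". The same section says that differences in the individual metrics ("primary outcome parameter) will be analyzed by Chi-squared test"). So there are seven primary comparisons of equal standing. The text names no lead metric, composite, ordering, significance level or adjustment, and no number of metrics that must differ.

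The Methods part of the abstract rests a single judgement on these comparisons: "Effectiveness of the intervention will be assessed by comparing the proportion subjects with ideal health metrics".

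The sample size statement begins "On the basis of a 3:1 intervention to control group split" and continues that "power analysis indicates that 95% power can be achieved with a sample size of 2000". The detectable differences are 3 points at a control proportion of 96% and 10 points at 50%. Each figure describes one comparison on one metric. The Study design section gives the group sizes as 1500 (intervention) and 500 (control).

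**The concern.** Seven tests feed one verdict on whether the programme works, and nothing says how to get from the tests to the verdict. Followed as written, a significant difference on any one metric could be reported as a positive primary result. A mixed outcome, with some metrics better and some worse, has no defined reading. The false-positive rate for the overall claim would then be well above the rate for a single test.

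The power statement has the matching weakness. If the seven tests are later adjusted, the 95% no longer holds for the stated differences. If they are not, the overall error rate is uncontrolled. The statement therefore needs attention whichever course the analysis takes.

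**Working it through.** **Inputs.** From the article: seven primary metrics, chi-squared test for each, 500 control and 1500 intervention participants, 95% power, 50% versus 60% and 96% versus 99%. Assumed: a two-sided 5% level per test, because none is stated, and independent participants.

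**1. Reproducing the stated power.** For two proportions with pooled variance under the null:

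power = Φ[(d − z·s0)/s1], where s0 = √{p̄(1−p̄)(1/500+1/1500)}, s1 = √{pC(1−pC)/500 + pI(1−pI)/1500} and p̄ = (500pC + 1500pI)/2000.

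- 50% versus 60%: p̄ = 0.575, s0 = 0.02553, s1 = 0.02569. At z = 1.960, (0.10 − 0.05003)/0.02569 = 1.945, so power is 97.4%.
- 96% versus 99%: p̄ = 0.9825, s0 = 0.00677, s1 = 0.00913. At z = 1.960, (0.03 − 0.01327)/0.00913 = 1.832, so power is 96.7%.

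Both meet the stated 95% with a little to spare. The same formula gives exactly 95% at a per-test level of about 0.024 (50% versus 60%) and 0.027 (96% versus 99%).

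**2. Which levels are compatible with the stated power?**

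| Two-sided level per test | 50% vs 60% | 96% vs 99% |
|---|---|---|
| 0.05 | 97.4% | 96.7% |
| 0.025 | 95.2% | 94.8% |
| 0.01 | 90.9% | 91.6% |
| 0.05/7 = 0.00714 | 88.9% | 90.2% |

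At 0.05/7, z = 2.690. For 50% versus 60% this gives (0.10 − 0.06867)/0.02569 = 1.219. For 96% versus 99% it gives (0.03 − 0.01822)/0.00913 = 1.290. Direct binomial simulation at this level gives 88.9% for the first case. For the second it gives 92.7% without and 89.7% with continuity correction. All are below 95%.

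**3. Differences detectable with 95% power at N = 2000.** Solving the same formula for d:

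- At a control proportion of 50%: 9.2 points at 0.05, 11.1 points at 0.05/7 (stated: 10).
- At a control proportion of 96%: 2.9 points at 0.05, 3.2 points at 0.05/7 (stated: 3).

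Holding the stated differences at 95% power under 0.05/7 would take about 2464 and 2456 participants in total, roughly 23% more than 2000.

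**4. False-positive rate over seven tests at two-sided 5%.** With independent metrics, any significant result has probability 1 − 0.95^7 = 30.2%, and a result favouring the programme has probability 1 − 0.975^7 = 16.2%. With equally correlated test statistics:

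| Common correlation | Either direction | In favour of the programme |
|---|---|---|
| 0 | 30.2% | 16.2% |
| 0.3 | 27.1% | 13.7% |
| 0.5 | 23.0% | 11.5% |

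Seven independent tests at 0.05/7 each would give 1 − (1 − 0.05/7)^7 = 4.9% in either direction.

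**The case against.** The strongest reply is that this is a condensed article and an analysis plan may exist. A multiplicity procedure could sit there without contradicting any sentence here. That is fair as regards the method of adjustment, and its absence alone would not be a finding. But the article itself fixes seven co-equal primary comparisons and a power figure that leaves no room for a seven-fold correction. An adjustment made elsewhere would leave the published 95% wrong for the stated differences.

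Three stronger readings are tempting, and the document does not support them:

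- A reader might infer that an ineffective programme has a 30% chance of being declared effective. The 30% assumes an unstated two-sided 5% level and independent metrics, and it counts results against the programme too. In the programme's favour it is about 16%, and less with positive correlation.
- A reader might infer from the power figure that an uncorrected 5% level must have been used. A level of 0.025 fits at least as well (95.2% and 94.8%). What can be excluded is a full seven-fold correction. Even at 0.025 per test, seven independent tests give 1 − 0.975^7 = 16.2% for a result in either direction.
- A reader might conclude that the primary outcome should be replaced by the number of ideal metrics per participant. That is a different design choice and is not needed to correct the problem.

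It is also true that the aims section lists several primary objectives, most of them descriptive, so effectiveness is not the trial's only question. It is, however, the question that the primary outcome is meant to answer. The loss of power is moderate, about 5 to 6 points below the stated figure.

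**Conclusion.** The point holds in a conditional form. The article sets up seven equal primary tests for one effectiveness claim, with no error control and no success rule, and quotes a power that is valid only metric by metric. At an assumed two-sided 5% per test, the chance of at least one false-positive primary result is up to 30% in either direction and about 16% in favour of the programme. Correlation of 0.3 to 0.5 brings these to 27–23% and 14–11.5%. Under a seven-fold correction, power is about 89–90% instead of 95%, and both stated differences fall short of what is detectable with 95% power, by 1.1 points (at 50%) and 0.2 points (at 96%). All figures treat participants as independent and use the full 2000. The defect should be corrected, but it does not undermine the sample size.

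**What to change.** Apply the Holm procedure across the seven primary metrics at an overall two-sided 5% level, and state that level. State that effectiveness will be claimed only for those metrics whose difference favours the programme and is significant after Holm adjustment. Restate the power at 0.05/7, the most stringent Holm step: about 89% for 50% versus 60% and 90% for 96% versus 99%. Alternatively, restate the differences detectable with 95% power as about 11.1 and 3.2 points. Because Holm relaxes the level after each rejection, these figures are a floor for any one metric.

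The cost is about one paragraph of text and a slightly less favourable stated detectable difference. No new data and no added participants are required.

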#### Inclusion criteria

Participants in the 10th to 12th grade (mean ages 15–16 at baseline for the intervention group and 17–18 years for the control group) will be enrolled. Informed consent by the participant and, for participants younger than 18 years, their legal representative will be obtained. Consent for inclusion of data from the “mother-child booklet” additional maternal informed consent will be obtained.

Schools and training companies will be randomly assigned to either the intervention or the control group. The examination of the intervention group will start first. Schools will be assigned to either group according to their available schedule. The exact number of participating schools/training companies will depend on the number of participants per school/company.

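### Schools and companies are assigned and treated as units, but the primary chi-squared test and the 95% power figure treat 2000 pupils as independent

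*Protocol article*

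**What the plan says.** All references are to the protocol article.

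- **Unit of assignment.** Under Inclusion criteria: "Schools and training companies will be randomly assigned to either the intervention or the control group". Shortly afterwards: "Schools will be assigned to either group according to their available schedule". The two sentences disagree on the mechanism, but in both the school or company is what gets assigned.
- **Number of units.** The same section leaves it open: "The exact number of participating schools/training companies will depend on the number of participants per school/company".
- **Unit of delivery.** The Intervention section describes a kick-off event at the school or company, class results set against those of other schools and companies, and a "tailored health promotion program for each school or company class". Individual counselling and an online tool run alongside.
- **Primary analysis.** Under Outcome measures and statistical analysis, differences in the proportion with each health metric in the ideal range between "the intervention and control group (primary outcome parameter) will be analyzed by Chi-squared test". Logistic regression is named for multivariable analysis, with no model terms given.
- **Power.** The same section states that "power analysis indicates that 95% power can be achieved with a sample size of 2000", split 3:1, for differences of 3 points at a control proportion of 96% up to 10 points at 50%.

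The article mentions no intracluster correlation (ICC), design effect, random effect, GEE or robust variance.

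**The concern.** Pupils at one site share a school type, a social setting and, in the intervention arm, a locally designed programme. The Discussion itself expects social background to vary across school types and apprentices. Smoking, diet, activity and weight are therefore likely to be more alike within a site than between sites.

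An ordinary chi-squared test takes its standard error from the number of pupils. When sites are assigned, the true standard error depends on the number of sites and on how much they differ, so the test's standard error is too small and its p-values too low. This applies to each of the seven primary comparisons in direction; its size may differ by metric. A power calculation on independent pupils has the same flaw. At stake are the false-positive rate of the main effectiveness claim and the credibility of the printed detectable differences.

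**Working it through.** **Inputs from the article:** 500 control and 1500 intervention participants; 96% to 99% (the 3-point case read as an increase) and 50% to 60%; 95% power.

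**Assumed, because not stated:** two-sided alpha 0.05; m pupils per site; a common ICC; no dropout.

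**Step 1: reproduce the stated power with independent pupils.**

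Power = Φ[(|p2 − p1| − 1.96·SE0)/SE1], where SE0 = √[p̄(1 − p̄)(1/500 + 1/1500)] and SE1 = √[p1(1 − p1)/500 + p2(1 − p2)/1500].

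- 50% vs 60%: p̄ = 0.575, SE0 = 0.02553, SE1 = 0.02569. (0.10 − 0.05004)/0.02569 = 1.945, so power is 97.4%.
- 96% vs 99%: p̄ = 0.9825, SE0 = 0.00677, SE1 = 0.00913. (0.03 − 0.01327)/0.00913 = 1.83, so power is 96.7% (95.4% with continuity correction).

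The stated 95% is thus met with independent pupils and no design effect, with little slack.

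**Step 2: how much clustering uses up the slack.**

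Design effect DE = 1 + (m − 1)·ICC; effective sizes are 500/DE and 1500/DE. Power reaches 95% at DE of about 1.13 (96% vs 99%) and 1.18 (50% vs 60%). At m = 50 the matching ICC is about 0.13/49 = 0.003 to 0.18/49 = 0.004. At m = 20 it is about 0.007 to 0.009.

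**Step 3: a range of assumptions.**

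Type I error of the unadjusted test = 2·[1 − Φ(1.96/√DE)]. Power is Step 1 at the effective sizes, that is, for a test that allows for the clustering.

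| m | ICC | DE | Type I error | Power 50% vs 60% | Power 96% vs 99% |
|---|---|---|---|---|---|
| 20 | 0.005 | 1.095 | 6.1% | 96.2% | 95.4% |
| 20 | 0.01 | 1.19 | 7.2% | 94.7% | 94.0% |
| 40 | 0.02 | 1.78 | 14.2% | 83.4% | 84.4% |
| 60 | 0.05 | 3.95 | 32% | 50% | 58% |

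Worked row, m = 40 and ICC 0.02: DE = 1 + 39 × 0.02 = 1.78. Effective sizes are 500/1.78 = 281 and 1500/1.78 = 843. 1.96/√1.78 = 1.469, so type I error is 14.2%. At 50%, the difference detectable with 95% power rises from about 9.3 to about 12.3 points.

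**Step 4: simulation check.** Beta-binomial simulation of the unadjusted chi-squared test under the null gave 0.138 for 12 vs 38 schools of 40 at ICC 0.02 (formula 0.142). For m = 50 and ICC 0.02 it gave 0.170 at a proportion of 50% and 0.157 at 96% (formula 0.164).

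**Limit of the calculation.** The control arm would hold about 500/60 ≈ 8 to 500/20 = 25 sites. A valid analysis with so few clusters loses further degrees of freedom, so the power figures above are somewhat optimistic.

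**The case against.** The strongest reply is that the size of the problem cannot be read from the article. ICC, cluster size, number of sites and alpha are all unstated; one ICC is applied to seven metrics that need not cluster alike; and the results run from slight to severe. That stands, and the figures are conditional for that reason.

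A second reply is that an unseen analysis plan may handle clustering. It could add a cluster term to the logistic regression, whose terms the article leaves open. It could not do so for the primary comparison without replacing the test the article names, and the printed power figure would still rest on independent pupils.

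A reader might also infer three stronger points that the article does not support:

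- **That 95% power is out of reach under any realistic correlation.** With 20 pupils per site and ICC 0.005, power is still 96.2% and 95.4%.
- **That the planned confidence intervals are too narrow.** The statistical section specifies a test and a regression, and mentions no interval.
- **That the type I figures are the trial's overall false-positive rate.** They cover clustering only. If schools are assigned by schedule, systematic differences between the groups' schools are a separate threat, which allowing for clustering does not remove.

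**Conclusion.** The point holds. The stated primary test and the stated power basis both ignore the unit of assignment, whichever assignment sentence applies. This is an error in what the article fixes, not a detail it leaves out.

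The direction is certain for any positive within-site correlation: the chi-squared test rejects too often. The size is conditional. Under the assumptions in the table, type I error runs from 6.1% to 32%. Power runs from just above the stated 95% down to 50% (50% vs 60%) or 58% (96% vs 99%). Moderate values (40 per site, ICC 0.02) give roughly 14% false positives per metric and 83% to 84% power. Because the number of sites is left open, nothing in the plan bounds the problem. It bears on the validity of the primary inference and should be corrected before analysis.

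**What to change.** 1. **Primary analysis.** Replace the chi-squared test with one pre-specified cluster-aware method that estimates the stated quantity, the difference in proportions. A suitable choice is a marginal GEE model with school or company as the cluster, a small-sample correction, and the result expressed as a difference in proportions. A cluster-level comparison of site proportions is an acceptable alternative; one of the two should be named.
2. **Logistic regression.** Allow for the same clustering there.
3. **Power paragraph.** State alpha, an ICC range, the expected cluster size and the number of sites per arm. Give the power or detectable differences that 2000 pupils then deliver, for example about 12.3 rather than 9.3 points at 50% if DE is 1.78.

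**Cost.** Revised wording and a less favourable power figure, with no added enrolment or visits. Examinations take place at the school or company (Data acquisition), so site membership should be recoverable, but the sponsor should confirm that it is recorded as an analysis variable. Keeping 95% power for the printed differences would be another matter: at m = 50 and ICC 0.02 (DE 1.98), the 1704 and 1780 pupils required under independence become 1704 × 1.98 = 3374 and 1780 × 1.98 ≈ 3525. Restating the power is the proportionate course.

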## Discussion

The EVA-Tyrol study is a large-scale research and prevention program targeting cardiovascular health-promotion in adolescents. The planed 2000 participants will represent about 5% of the Tyrolean population at that age and will allow in-depth insights into vascular risk profile and vascular health of a representative Middle European population. The health promotion program used in our trial could realistically be continued at low costs outside the academic study setting. Our study explores novel grounds, as, even though numerous health promotion programs are targeted to the youth, few did prove efficacy. The STRIP study conducted in Turku, Finland, was able to increase the number of ideal cardiovascular health metrics by accompanying children with dietary and later smoking prevention counselling continuously between the age of 7 month and 20 years. Also, dietary counseling of pre-pubertal children with elevated LDL Cholesterol and their parents effectively reduced LDL Cholesterol [34]. However, other health promotion programs for adolescents were less successful [32, 35]. A recent meta-analysis of 30 studies aiming at improving physical activity in children and adolescents could demonstrate only a modest effect of various interventions [35]. In contrast to our study all these interventions focused on a single health behavior and did not provide comprehensive health counseling on multiple cardiovascular risk factors and behaviors.

The descriptive analysis of the EVA-Tyrol study will substantially enhance our understanding of the distribution of vascular risk behaviors and risk factors in subjects with varying social backgrounds (school types, apprentices) as well as sex and age groups and will help to better focus future health promotion programs.

Furthermore, the EVA-Tyrol cohort will allow to explore mechanisms of early vascular ageing by using well-defined surrogate parameters for vascular health (IMT and PWV) and analyze their association with cardiovascular risk factors and health behaviors. High-quality information from the “mother-child booklet” will elucidate the impact of early life weight gain on adolescent vascular health.

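### The primary comparison of a non-randomised trial is an unadjusted chi-squared test, so differences between arms in school type, sex or region can pass for, or hide, a programme effect

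*Protocol article*

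**What the plan says.** All places are in the protocol article.

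- **Design** (Study design): "The EVA-study is a non-randomized controlled trial". Only the intervention group is examined twice, in the 10th and 12th grades. Controls are enrolled in the 12th grade, so they have no baseline.
- **Assignment** (Inclusion criteria): "Schools and training companies will be randomly assigned to either the intervention or the control group". This is followed by "The examination of the intervention group will start first" and "Schools will be assigned to either group according to their available schedule".
- **Primary outcome** (Outcome measures and statistical analysis): "the difference in the proportion of each of AHA’s seven health metrics in the ideal range between the intervention and the control group".
- **Primary test** (same section): differences between "the intervention and control group (primary outcome parameter) will be analyzed by Chi-squared test". No covariate or stratification is named.
- **Adjusted analysis** (same section, last sentence): "Multivariate analysis will be done by logistic regression". Its outcome, its covariates and its standing relative to the primary test are not given.
- **Expected heterogeneity** (Discussion): risk behaviours and risk factors are to be described in "subjects with varying social backgrounds (school types, apprentices"), and by sex and age group.
- **Regions** (Recruitment): two study centres, one in Austria and one in Italy.

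**The concern.** A crude comparison of proportions estimates a programme effect only if the arms are alike in everything else that affects the metrics. Here whole schools and companies are placed in an arm according to when they are available. The protocol describes no matching or stratified assignment. The controls have no earlier examination against which to check or correct an imbalance. The Discussion itself names school type, apprenticeship and sex as dimensions along which risk is expected to vary.

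The trial's central claim, that the programme works, rests on this comparison. If the intervention arm contains a larger share of pupils from school types with better metrics, the chi-squared test can report that mix as effectiveness. If the imbalance runs the other way, a real effect can be missed. If the crude and adjusted results disagree, the text as written gives priority to the crude one.

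**Working it through.** **1. Is the crude test really the planned primary analysis?** The power statement gives 95% power with 2000 participants, split 3:1, to detect 3 points at a control proportion of 96% and 10 points at 50%. The significance level is not stated, so I assume two-sided 0.05.

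For an unadjusted comparison of two proportions, with n0 = 500, n1 = 1500 and d the difference:

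- s0 = √[p(1−p)(1/500 + 1/1500)], where p is the pooled proportion
- s1 = √[p0(1−p0)/500 + p1(1−p1)/1500]
- power ≈ Φ[(d − 1.96·s0)/s1]

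96% vs 99%: p = 0.9825, s0 = 0.00677, s1 = 0.00913. (0.03 − 0.01327)/0.00913 = 1.83, so power is **96.7%**.

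50% vs 60%: p = 0.575, s0 = 0.02553, s1 = 0.02569. (0.10 − 0.05003)/0.02569 = 1.945, so power is **97.4%**.

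Both reach the stated 95%. The power figure is not in dispute, and it shows that the sample size fits the unadjusted test.

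**2. What can an imbalance do to that test?** Take one binary factor, such as apprentice versus school pupil, and no programme effect. Then:

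spurious difference = (difference between arms in the factor's share) × (difference in ideal prevalence between its two levels)

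The documents give neither quantity, so both are assumptions and are shown as a range. The rejection probability uses the formulas above with a control proportion of 50%, counting both tails.

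| Share imbalance (points) | Prevalence gap (points) | Spurious difference (points) | Probability of p < 0.05 |
|---|---|---|---|
| 5 | 10 | 0.5 | 5.4% |
| 10 | 20 | 2 | 12.1% |
| 20 | 15 | 3 | 21.4% |
| 20 | 25 | 5 | 49.3% |
| 30 | 25 | 7.5 | 83.1% |

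Worked line for 5 points: p = 0.5375, s0 = 0.02575, s1 = 0.02579. (0.05 − 0.05046)/0.02579 = −0.018, and Φ(−0.018) = 49.3%.

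**3. Does this range hold for all seven metrics?** No. The protocol cites a similar cohort with ideal diet below 5%, ideal physical activity around 50% and ideal body-mass index above 80%. At 5% overall, a 25-point gap requires one stratum to be at 25% or more. That stratum could then hold at most 5/25 = 20% of pupils, with all others at zero. Large gaps are therefore implausible near the extremes. On the other hand, s0 at 5% is √(0.05 × 0.95 × 0.002667) = 0.0113, against 0.0258 at 50%, so a given point difference is detected more easily there. The table applies to prevalence near 50% only.

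**The case against.** **Randomisation is mentioned.** The Inclusion criteria section does say that schools and companies are randomly assigned. This conflicts with the title, with the Study design section and with the schedule-based rule in the same paragraph, so it cannot be relied on and the statements must be reconciled. Even random assignment of a modest number of whole schools would not secure balance in school type.

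**Adjustment is foreseen.** Logistic regression suits a binary ideal/not-ideal outcome, and the sentence follows the primary comparison and its power statement in the same paragraph. Leaving its covariates to a fuller plan is normal and is not criticised here. A reader might infer that the protocol ignores confounding altogether, which would be wrong. What stands is narrower: the document itself chooses the crude test for the primary outcome, and the regression could equally serve the exploratory analyses.

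**Schools did not choose their arm.** A reader might infer from the application process that two self-selected sets of schools are compared. Under Recruitment, schools apply for inclusion in the study, a step common to both arms. Only the schedule rule bears on which arm a school enters. The same section aims for an even regional and social spread, but of the sample as a whole, not between arms.

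**Age.** It is tempting to add age to the list of imbalances. Both arms are compared in the 12th grade at mean age 17–18, so the documents do not support age as a main source of bias.

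**The imbalances are assumed.** This stands. Mild imbalance does little harm (5.4% and 12.1% in the first two rows).

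**Conclusion.** The point holds in this form: the protocol fixes an unadjusted test as the primary analysis in a design that does not secure comparable arms, and the one sentence on regression does not change which result decides. Differences in school type or apprenticeship, sex or region can therefore be reported as, or can hide, a programme effect.

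The documents do not support saying that this will happen. They give no covariate distribution by arm, so the size and direction of any imbalance are unknown. Under the illustrative assumptions (no programme effect, one binary factor, prevalence near 50%, two-sided 0.05), the false-positive rate for one metric runs from about 5% with slight imbalance to about 83% with strong imbalance. The defect matters because it bears on the main effectiveness claim and nothing in the design keeps the imbalance small.

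**What to change.** 1. For each metric, make the primary estimate the between-group difference in the proportion ideal, derived from a logistic regression on arm with prespecified covariates: school type/apprenticeship, sex, region, and the age and social-background data already collected. Use standard errors that allow for school or company.
2. Keep the chi-squared test as an unadjusted supporting analysis.
3. Reconcile the random-assignment sentence with the schedule rule and the non-randomised label.
4. Word the conclusion as an association adjusted for measured confounders.

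No new data are needed. School, sex, age and region are inherently known, and the questionnaire covers social background (Table 1). The cost is slightly more analysis work and possibly somewhat wider intervals. Confounding by unmeasured factors remains, regression on 12th-grade covariates does not replace the missing control baseline, and a school type found in only one arm cannot be separated from the programme by any model.
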